All permanent residents of the target communities meeting the inclusion and exclusion criteria will be eligible for inclusion in the cohort. Permanent residents meeting these criteria will be identified from the registers of residents in community health centers (which list virtually all permanent community members). Initially 3250 eligible individuals will be randomly selected from the lists of residents: after listing all adult eligible residents the total number of listed residents is divided by 3250 and the resultant integer and its fractional component (x.yy) are used to assess the proportion of the total list from which each x^th^ individual should be selected and the proportion of the total list from which each (x + 1)^th^ individual should be selected to arrive at a total sample of 3250. As many of these individuals as possible will be recruited into the project, even if the number of enrollees exceeds the minimum required sample of 2500 individuals. If contacting the 3250 eligible individuals does not result in enrolling 2500 individuals, an addition number of individuals from the resident list who were not selected the first time will be randomly selected in the same manner and invited to participate (considering the potential non-response rate of 30%, the additional number will be defined as 1.3 times of the differences between 2500 and actual number); this process will be repeated as needed until 2500 individuals have been enrolled. Reasons for non-enrollment and for post-enrollment drop-out will be described and the potential effects of selective enrollment and dropouts on the representativeness of the sample will be assessed by comparing the demographic characteristics of enrolled individuals with those of individuals who are selected for recruitment but not enrolled and of persons who drop out after enrollment with those of individuals who continue in the cohort.

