#### Sample size

Based on a previous cross-sectional epidemiological study, the prevalence of major depressive disorder among adults in China was 2.1% [33]. Using version 15.0 of the Power Analysis & Sample Size (PASS) package, a sample size of 79,986 is required to identify a condition with a prevalence of 2.1% with a 95% confidence interval of 2.0% to 2.2%. We conservatively decided on a total target cohort of 85,000. This sample will be equally divided between the 34 sampled communities, that is, 2500 individuals in each community. Considering a potential non-response rate of 30% [34], the baseline recruitment will approach at least 3250 adults in each community. Individuals who are lost to follow-up after enrollment will be replaced annually by other individuals who live in the same community, maintaining the cohort size to a minimum of 2500 individuals at each primary sampling site throughout the 5 years of the project.

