#### Follow-up

The initial duration of follow-up is five years. (The study organizers will subsequently apply for additional funding to transform the study into a continuing cohort project.) The follow-up procedures will be as follows:A)Community-level variables shown in Table 2 (including climatic, environmental and socio-economic characteristics) will be collected annually from national databases for each of the 34 primary sampling sites.B)Participants who do not have any current or past mental disorder (based on the SCID-5-CV interview) at baseline or at subsequent assessments, the following follow-up assessments will be made *annually*.Information about participants’ diagnoses and treatment of diseases in the prior year will be collected in three ways: review of records of the national medical insurance system (which covers all permanent residents); self-reported information about medical treatment for mental disorders; and results of the annual GHQ-12 screening and SCID-CV interviews.Community clinic physicians conduct a physical exam, measuring weight, heart rate and blood pressure.Research nurses collect biological samples of blood, urine and faeces from a sample of 5% of the participants.Repeat MRI scans we be conducted in each participant who had MRI scan at baseline.Online questionnaires will be sent to participants through e-mail or WeChat. Participants unable to use this online system will be invited to visit the local health clinic where they will be given equipment and any assistance needed to complete the questionnaires.Trained researchers will make phone calls to those who don’t respond to the online questionnaires and to those who self-report as being at high risk of a depressive disorder at any time over the prior year. Participants classified by the researcher as ‘high-risk of depression’ at any time in the prior year will be encouraged to attend an appointment with a psychiatrist at the community clinic or local general hospital.Psychiatrists will perform SCID-5-CV diagnostic assessments of the invited participants who agree to the interview.C)For participants diagnosed with current or past depressive disorder or other psychiatric disorder based on SCID-5-CV interviews by a psychiatrist at baseline or during follow-up assessments the following follow-up assessments will be conducted.Every 3 months, telephone calls will be performed by trained researchers to check their depressive symptoms, thoughts of suicide or self-harm, suicide attempts or other self-harm behaviors, social functioning, and mental health treatments over the prior 3 months. Individuals classified by the researcher as ‘high-risk of depression’ who have never been diagnosed with a depressive disorder (only had other diagnoses) or have fully recover from a prior episode of depression (i.e., at least 2 months of no clinically significant symptoms) will be encouraged to attend an appointment with a psychiatrist at the community clinic or local general hospital.A psychiatrist will conduct a repeat diagnostic exam (using the SCID-5-CV interview) with invited participants who agree to the interview to determine whether a new-onset major depressive disorder has occurred in the prior 3 months.Each year information about participants’ diagnoses and treatment of diseases (including treatment for mental disorders) from hospital records will be collected from regional hospitals and from the national public health system.Each year community clinic physicians conduct a physical exam, measuring weight, height, heart rate and blood pressure.Each year the standard online questionnaire will be sent to these participants through e-mail or WeChat. Participants unable to use this online system will be invited to visit the local health clinic where they will be given equipment and any assistance needed to complete the questionnaires.Each year research nurses collect biological samples of blood, urine and faeces from participants with a current or lifetime depressive disorder (but NOT from individuals who only have other, non-depressive, mental disorders).Each year, participants with a current or lifetime depressive disorder (but NOT from individuals who only have other, non-depressive, mental disorders), are referred for a brain MRI scan at a regional hospital.

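### Annual replacement keeps the headcount but neither restores lost follow-up nor corrects depression-related loss, and the stated drop-out check covers demographics only

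*Protocol article*

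**What the plan says.** **Sample size.** The article takes it that "the prevalence of major depressive disorder among adults in China was 2.1"% and states that "a sample size of 79,986 is required to identify a condition with a prevalence of 2.1% with a 95% confidence interval of 2.0% to 2.2"%. It continues: "We conservatively decided on a total target cohort of 85,000". The phrase "Considering a potential non-response rate of 30"% concerns recruitment, not later attrition. For loss after enrolment the rule is that "Individuals who are lost to follow-up after enrollment will be replaced annually by other individuals who live in the same community". Its stated purpose is "maintaining the cohort size to a minimum of 2500 individuals at each primary sampling site throughout the 5 years of the project".

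**Sampling method.** Reasons for non-enrolment and for drop-out will be described. Selective enrolment is to be assessed by "comparing the demographic characteristics of enrolled individuals with those of individuals who are selected for recruitment but not enrolled". The same sentence applies the same demographic comparison to drop-outs against those who stay.

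**Follow-up.** "The initial duration of follow-up is five years". Outcome information comes from yearly screening and SCID interviews, self-report, and review of insurance or hospital records.

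**Data analyses.** The plan covers prevalence, incidence and trends, with poststratification weights for the national estimates, and Cox regression for risk factors.

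**The concern.** The study is sized for a cross-sectional proportion, but its main outcome is the occurrence of depressive disorders over time. Refilling each site suits repeated prevalence estimates. For incidence and hazard ratios, what counts is whether the people who leave differ in depression risk from those who stay. A replacement arrives later, has shorter follow-up, and says nothing about the outcome of the person who left.

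Depression-related loss is plausible here. Case finding relies on answering questionnaires or calls and then agreeing to an interview. The stated check could miss such loss, because drop-outs and continuers may match on demographics and still differ in baseline symptoms. The baseline assessment includes the expanded GHQ-12 and PHQ-9, and SCID interviews are done in all high-risk, 40% of moderate-risk and 10% of low-risk participants. None of these enters the stated comparison. Poststratification weights correct loss only as far as it depends on the weighting variables.

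**Working it through.** **1. The plan's own figure.** Inputs from the Sample size section: p = 0.021, half-width h = 0.001, 95% confidence. The exact (Clopper-Pearson) interval with total width 0.002 needs n = 79,985.3, which rounds up to the stated 79,986. The simple Wald formula, 1.96² × 0.021 × 0.979 / 0.001², gives 78,977. The target is 34 × 2,500 = 85,000. The figure is correct for a prevalence. It contains no term for loss during follow-up.

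**2. What replacement keeps and what it does not.** The annual loss d is not stated, so a range is assumed. Original members with full 5-year follow-up: 85,000 × (1 − d)^5. Share of completed annual assessments that come from replacements: 1 − [Σ(1 − d)^k, k = 1 to 5] / [5(1 − d)].

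| Assumed d | Originals followed 5 years | Share of 85,000 | Assessments from replacements |
|---|---|---|---|
| 5% | 65,771 | 77% | 10% |
| 10% | 50,192 | 59% | 18% |
| 15% | 37,715 | 44% | 26% |

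For d = 10%: 0.9^5 = 0.590, and 1 − 3.686/4.5 = 0.181. The nominal size is 85,000 in every row. Replacements have at most 4 years of follow-up.

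**3. Incidence under informative loss (all inputs assumed).** Let λ be the annual risk, d the loss in non-cases and r·d the loss in that year's new cases. With no recovery from records, the observed annual risk is

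λ(1 − rd) / [λ(1 − rd) + (1 − λ)(1 − d)].

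With λ = 0.01, d = 0.10, r = 2: 0.008 / (0.008 + 0.891) = 0.0089. The 5-year risk is then 1 − (1 − 0.0089)^5 = 4.37%, against a true 1 − 0.99^5 = 4.90%. The ratio is 0.89, about 11% low. The short form 0.80/0.90 = 0.889 agrees.

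| Loss in non-cases | r = 1 | r = 1.5 | r = 2 | r = 3 |
|---|---|---|---|---|
| 5% | 4.90% | 4.78% | 4.65% | 4.40% |
| 10% | 4.90% | 4.64% | 4.37% | 3.84% |

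If replacements share the same λ, d and r, they multiply observed cases and observed non-cases by the same factor. That factor cancels, so replacement leaves every entry unchanged.

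**4. Hazard ratios.** Take a true HR of 1.5 and λ = 0.01 in the unexposed. If case-related loss is equal in exposed and unexposed, the estimate stays at 1.50. If only exposed cases are lost r = 1.5, 2 or 3 times as often, it falls to 1.42, 1.33 or 1.17 at 10% loss, and to 1.46, 1.42 or 1.34 at 5% loss.

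**The case against.** **Attrition is not hidden.** A reader might infer that refilling makes retention look complete. The Sampling method section does not support that: it promises reasons for drop-out and a comparison of drop-outs with continuers. Nothing says that headcount will be reported as retention or that replacements will be pooled unmarked.

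**Replacement does not cause the bias.** This is right. The 11% in step 3 arises with or without it. Refilling is a sensible way to hold prevalence precision, and replacements add valid person-time from their own entry date.

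**Some outcomes may be recovered.** The Follow-up section plans yearly review of insurance records covering all permanent residents, and calls to questionnaire non-responders. This is a real safeguard, but a partial one. Records capture diagnosed or treated illness, and the article does not say whether review continues after a person is lost and replaced.

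**The size is assumed.** No attrition rate is given. The 94% willing to accept follow-up in the pilot is stated willingness, not retention.

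**Analysis detail may lie elsewhere.** Flags, delayed entry and weights are commonly left to a full protocol or analysis plan, and their absence from the article is not a fault. The two stated choices remain open to comment: refilling as the response to loss, and a drop-out check limited to demographics.

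**Conclusion.** The point holds in a limited form. Annual replacement maintains numbers and prevalence precision. It does not recover the follow-up of original members or correct loss related to depression, and a demographics-only comparison is too narrow to detect such loss.

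Incidence is biased only if loss relates to depression beyond the analysis variables. Over the assumed scenarios with excess loss in cases, the 5-year risk is about 3% to 22% low in relative terms (4.78% to 3.84% against 4.90%), and about 11% low at 20% versus 10% annual loss. These figures assume no recovery from records and are illustrations, not forecasts.

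A reader might go further and infer that the hazard ratios are necessarily biased, or that replacements must leave the primary analysis. Neither follows. Hazard ratios shift only if depression-related loss also differs by exposure. Dropping replacements would remove none of the bias and would discard about 18% of completed assessments at 10% annual loss, which on a simple count basis widens intervals by about 10% (1/√0.819 = 1.10).

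**What to change.** - Extend the drop-out comparison in the Sampling method section to baseline GHQ-12 risk group, PHQ-9 and, where an interview was done, SCID diagnosis.
- Use these variables, with demographics and site, in inverse-probability-of-censoring weights for the incidence and Cox analyses, at least as a pre-specified sensitivity analysis.
- Keep replacements in the analysis from their own entry date.
- Report retention of the original cohort separately from the refreshed headcount.

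If a fuller protocol or analysis plan already covers the second and third items, a cross-reference is enough.

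The cost is a little more analysis work and slightly wider weighted confidence intervals. The baseline variables are already collected. The weights correct loss only as far as measured baseline variables explain it. Loss driven by a new episode that baseline data do not predict would remain, so the weighted result should be presented with that limit stated.

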### Procedures

Participants will complete online self-report questionnaires about their history and current status and undergo physical and psychological assessments at local community health centers; some of these participants will also receive brain MRI scans at regional general hospitals. Details about the content and method of the evaluations are shown in Table 1.

**Table 1 Tab1:** Data collected from individual participants

TYPE OF DATA Instrument(s) Collection method	Variables
**DEMOGRAPHIC CHARACTERISTICS** Self-report questionnaire designed by researchers Participants finish the questionnaire online while visiting a local community health clinic	1. **Age:** Age at the day of data collection
	2. **Gender**: Biological sex registered on the ID card (male or female)
	3. **Ethnicity**: Ethnicity registered on the ID card (Han, Miao and so forth)
	4. **Siblings:** Twins, triplets or other siblings with the same parents
	5. **Marital status**: Marriage status at the day of data collection, categorized as single, married, cohabiting with significant other, divorced, widowed, and other
	6. **Education level:** The highest education level, categorized as primary school, middle school, high-school, university and above
	7. **Religion**: Categorized as None, Buddhist, Christian, Islam, Catholicism and other
	8. **Health insurance**: Type of health insurance
	9. **Income**: Family income per year
	10. **Living status:** Living situation such as “where do you live”, “how many roommates” and etc
**PHYSICAL PARAMETERS** Assessed by health workers Participants evaluated at local health clinic	**11. Height**

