### Study population

#### Sample criteria

Chinese citizens 18 years of age or older currently living in the selected communities who are registered permanent residents of the community (i.e., whose formal household registration is in the community) will be potential participants. Individuals who are transient residents, citizens of foreign countries, and persons living in institutional settings (chronic-care hospitals, boarding schools and universities, factories, prisons, etc.) will be excluded from the sampling frame.

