#### Sampling method

We will use a multistage stratified random sampling method to identify 17 urban and 17 rural primary sampling sites in 17 of the 31 province-level administrative regions (hereafter, ‘provinces’) in mainland China. The 31 mainland provinces were first stratified by China’s seven administrative regions (Northeast, North, Northwest, East, Central, South and Southwest China) and then specific provinces from all seven geographic regions were selected to be nationally representative of the economic level and population size of the 31 different provinces. The 17 selected provinces included Heilongjiang and Liaoning from Northeast China; Beijing, Hebei, Tianjin, and Shanxi from North China; Gansu, Shanxi and Xinjiang from Northwest China; Zhejiang and Shanghai from East China; Henan, Hunan and Hubei from Central China; Guangdong from South China; and Sichuan and Chongqing from Southwest China.

Within each selected province, the second stage of sampling relied on China’s Disease Surveillance Points (DSP) System, a national representative sampling frame developed by the National Health Commission of the People’s Republic of China starting in 1978 that uses a stratified cluster random sampling method to select surveillance points (i.e., geographic areas that typically includes multiple communities or neighborhoods) around the country [30]. By 2021, a total of 605 points from all 31 provinces were included in this system, with a combined population of over 300 million individuals [30]. The disease surveillance points system provides a nationally representative cohort that has been widely used in national studies about the mortality and morbidity of various diseases [31, 32]. The number of DSP in the 17 selected provinces ranged from 7 (in Tianjin, Beijing and Shanghai) to 27 (in Heilongjiang). The DSP in each province were first stratified as urban or rural (based criteria specified by the National Bureau of Statistics) and then one urban and one rural DSP was selected for each province, resulting in a total 34 DSP. The criteria for selecting DSP within a province included 1) having a mean age of community members similar to that of all urban residents or all rural residents in the province; 2) having qualified mental health providers who were willing to participate in the management of the project; and 3) availability of MRI equipment needed to conduct the imaging part of the assessment.

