## Quality control

The members of the quality control committee include the lead collaborators and study managers at the 17 institutes, senior researchers on the project’s consultative committee, and staff members of the ethics committee at the Second Xiangya Hospital, Central South University. The Second Xiangya Hospital, Central South University is the lead institute of the China Depression Cohort Study-I, responsible for study design, national training, quality control, database management and primary data analyses.

The study procedures comply with national policies regarding the requirements of human studies. To ensure the consistency of the study in different settings, local pilot studies will be conducted to assess the feasibility of the proposed study procedures at all 34 primary sampling sites, and the procedures will be revised as needed based on the findings of the pilot studies. The specific goals of the pilot studies are to 1) identify methods for increasing enrollment and retention of participants, 2) develop methods for helping elderly participants complete online assessments, 3) test the effectiveness of the quality control and data entry procedures, 4) ensuring that sufficient numbers of rural participants (who may live far from hospitals that conduct MRI assessments) complete the brain MRI scans, and 5) develop uniform parameters for conducting the brain MRI scans at all participating general hospitals.

Once the formal study starts, local compliance with study procedures will be assessed during quarterly online meetings of the quality control committee to discuss and resolve problems that arise. Data collected at the 34 primary sampling sites will be checked in real time using the online project management system. Irregular, semiannual on-site inspections by project consultants and technical staff from the quality control committee will assess local study progress, observe the sample recruitment and data collection procedures, and check the methods of data entry, storage, and analyses.

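### The education item in Table 1 has no level below primary school, so adults without schooling have no correct code and cannot be told apart from those with primary schooling

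*Protocol article*

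**What the plan says.** In the Procedures section, Table 1 lists the individual-level data. Item 6 gives education as "The highest education level, categorized as primary school, middle school, high-school, university and above". The list is open at the top and closed at the bottom.

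Two neighbouring items in the same block are built differently. Religion is "Categorized as None, Buddhist, Christian, Islam, Catholicism and other", with both an explicit none and a residual option. Marital status is "categorized as single, married, cohabiting with significant other, divorced, widowed, and other", also with a residual option.

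Under Sample criteria the target group is "Chinese citizens 18 years of age or older currently living in the selected communities" who are registered permanent residents. Transient residents, foreign citizens and people in institutions are excluded. No criterion concerns age above 18, literacy or schooling. The Sampling method section sets out to "identify 17 urban and 17 rural primary sampling sites", and the Sample size section adds: "This sample will be equally divided between the 34 sampled communities, that is, 2500 individuals in each community". The Quality control section expects older participants, since one pilot goal is to "develop methods for helping elderly participants complete online assessments".

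**The concern.** A categorical item should give every eligible person exactly one true answer. For an adult who never went to school, item 6 gives none. That person is either recorded as primary school, which is wrong, or has no value.

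The stakes lie in the secondary layer of the study. The Aims section sets out to find risk factors for depression across biological, psychological and social domains, and the Data analyses section plans Cox models and prediction tools on such factors. Education is one of the collected social characteristics. If its two lowest levels are merged at collection, no analysis can separate them. The Sampling method section also plans to compare the demographic characteristics of drop-outs and continuers, and on education that comparison would have the same blind spot.

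**Working it through.** The point is a check that the categories are complete, so no statistical formula decides it. The article's one derived figure, the sample size of 79,986, reproduces exactly with a Clopper-Pearson 95% interval of total width 0.002 at a prevalence of 2.1% (solution 79,985.3, rounded up). Nothing below depends on it.

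**Step 1: is the list closed?** Where Table 1 shortens a list it says so. Ethnicity (item 3), living status (10), chronic pain (16), lifestyle (32), childhood exposures (33), life events (35) and childbearing history (36) all carry an open-ended marker. Item 6 carries none. Items 5 and 7 end in a residual option; item 6 does not. As printed, the four levels are the whole set.

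**Step 2: are the people it omits eligible?** Yes. There is no upper age limit, no schooling criterion, and half the sites are rural:
- rural target: 17 × 2,500 = 42,500
- total target: 34 × 2,500 = 85,000
- rural share: 42,500 / 85,000 = 50%

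**Step 3: how many?** The documents do not say. As an assumption only, for a share of rural participants without schooling:

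| Assumed share of rural participants | Number (× 42,500) |
|---|---|
| 1% | 425 |
| 5% | 2,125 |
| 10% | 4,250 |
| 20% | 8,500 |

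**Step 4: what does merging do?** Let p0 be the share of the cohort without schooling and pp the share at primary level. The unschooled make up s = p0 / (p0 + pp) of the merged category. If their risk is RR times that of the primary group, the merged category shows 1 + (RR − 1) × s times the true primary risk. With p0 of 3% to 10%, pp of 20% to 25% and RR = 1.5, all assumed:
- smallest s: 0.03 / (0.03 + 0.25) = 0.107, giving 1 + 0.5 × 0.107 = 1.05
- largest s: 0.10 / (0.10 + 0.20) = 0.333, giving 1 + 0.5 × 0.333 = 1.17

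The contrast between no schooling and primary is invisible, and the apparent risk of the primary level rises by 5% to 17%. What is lost is resolution at the bottom of the scale.

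**The case against.** The strongest reply is that Table 1 is a summary in a journal article and the questionnaire itself is not shown. The table is visibly condensed: it does not name the GHQ-12, the main screening tool. The online form may have a lower level, or may treat primary school as primary or below. This stands as a limit on what can be concluded. It does not remove the point, because item 6 states its categories as complete. A primary-or-below reading would cure the blanks but not the merging.

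It is also fair that education is never named as a covariate, predictor or weighting variable. Its role follows from the stated aim and the general reference to bio-psycho-social factors. For the comparison of enrolled with non-enrolled people, education may not be available at all, since the registry fields given as examples are name, age, address and phone number. The drop-out comparison does not have that difficulty.

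A reader might infer more serious consequences, which the documents do not support:
- **Census margins could not be matched in poststratification.** If unschooled adults are recorded as primary, the two census classes can be summed. No weighting variables are named in any case.
- **Older rural participants would drop out of complete-case models.** No complete-case method is stated, and trained researchers supervise completion of the baseline questionnaires.
- **The information would be lost for good.** Questionnaires go out annually and lack of schooling is largely fixed in adults, so it can be asked again of everyone still in follow-up.
- **The education gradient would simply be diluted.** If the unschooled carry the higher risk, merging raises the apparent primary-level risk and so widens its contrast with the higher levels.

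**Conclusion.** The point holds as a minor one. Followed as printed, item 6 gives unschooled adults no correct code in a cohort that admits them, and the study cannot then distinguish no schooling from primary schooling. The effect is confined to education as a social risk factor and to the drop-out comparison. Case definition, sampling, the primary outcome and the sample size are untouched.

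The size is unknown. The counts and the 5% to 17% range above rest on assumed shares and an assumed risk ratio; they illustrate the mechanism and do not show that the problem is large. The conclusion also assumes that the online form matches Table 1.

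**What to change.** Add *no formal schooling* as an option below *primary school* in the Participant Module before formal baseline enrolment. The timing is convenient: the Current status section reports local pilots at all 34 sites from March 2023, and the Quality control section allows procedures to be revised on pilot findings. For anyone already entered, ask the item at the next annual questionnaire; only those who leave before then would be missed. If the form already has such a level, correct Table 1 to show it.

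The cost is one extra response option. Analysts can still collapse it into primary where numbers are small or an external classification requires it.
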